#### Non-inferiority

The study has two primary outcome measures, each with caregiver and youth self-report versions (SCAS-c/p and CALIS-c/p). For each of the two scales a non-inferiority limit was determined based on an assumed difference in effect size of 0.1 between the interventions. This is the average ES found between two active preventive interventions with anxious youth [26]. Based on an effectiveness study of CBT for anxious youth in Norway [67], a SD of 14 will be applied for the SCAS-c/p post-intervention scores. With a difference in ES = 0.1, a non-inferiority bound is set to 1.4. This means that if the difference in post score in SCAS between VAAG and CHILLED is ≤1.4 in a one-sided test with α = 0.025, then VAAG will be found non-inferior to CHILLED on the SCAS scale. For CALIS-c/p (anxiety interference on child’s life), the non-inferiority bound is set to 0.7, based on results from an RCT efficacy study with anxious youth in Denmark [31] where an SD = 7 was found on CALIS c/p. Furthermore, to conclude that VAAG is non-inferior to CHILLED, three out of four primary outcome measures (SCAS-c/p and CALIS-c/p) have to be declared non-inferior.

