## Abstract

**Background:**

Anxiety disorders are prevalent among adolescents and may have long-lasting negative consequences for the individual, the family and society. Cognitive behavioral therapy (CBT) is an effective treatment. However, many anxious youth do not seek treatment. Low-intensity CBT in schools may improve access to evidence-based services. We aim to investigate the efficacy of two CBT youth anxiety programs with different intensities (i.e., number and length of sessions), both group-based and administered as early interventions in a school setting. The objectives of the study are to examine the effects of school-based interventions for youth anxiety and to determine whether a less intensive intervention is non-inferior to a more intensive intervention.

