## Methods

### Study design

This is a RCT with groups of 5-8 adolescents (12-16 years) allocated to two school-based CBT interventions and a control condition: (1) a brief intervention developed for the present study (VAAG), (2) a longer, more established intervention (CHILLED) and (3) a delayed access waitlist control group (WLC). Participants allocated to the two active interventions will start after a group of 5-8 adolescents has been assembled and randomized. Both interventions last for 10 weeks, VAAG comprises five sessions and CHILLED ten sessions. In addition CHILLED has two separate parent sessions. The expected number of hours of face-to-face professional contact is 18 h for the Chilled program and 5.5 h for VAAG. The waitlist group will be randomized in groups of 5-8 adolescents. Those allocated to the waitlist group will be randomized a second time to either VAAG or CHILLED after a delay of 10 weeks. Based on previous research, CBT early intervention for anxious youths is expected to be efficacious [26, 27]; therefore, we consider it unethical to withhold the intervention for adolescents allocated to the waitlist group for an extended period. Participants from all three conditions will be invited to a 1-year follow-up assessment. The overall study design is illustrated in Fig. 1, whereas the stages of the enrollment, interventions and assessments can be seen in Additional file 1: Figure S1 (The SPIRIT table).

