### Statistical analyses

#### Power calculation

Power calculations for differences among the three conditions, taking into account two repeated measurements with an assumed correlation of 0.6, yielded a required total sample size (power = 0.80, alpha = 0.05) of 294 children to obtain an effect size (ES) of 0.40. With an assumed attrition of 10%, we need to recruit 323 participants. Even though an average effect size in targeted prevention studies is 0.32 [26], we expect a somewhat larger effect size compared to WLC since we have included an intervention that has shown moderate to large effect sizes in previous studies when delivered as treatment or as a targeted preventive school intervention [31–33].

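### The 0.1 SD non-inferiority margin is not justified as an acceptable loss, and about 98 per arm gives roughly 10% power per outcome if the two programmes are identical

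*Protocol article*

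**What the plan says.** The abstract lists among the objectives "to determine whether a less intensive intervention is non-inferior to a more intensive intervention". The Objectives section makes this the second aim and the second main research assumption, and the Discussion makes non-inferiority a precondition for the brief programme's practical advantages to count.

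The Non-inferiority section says that "a non-inferiority limit was determined based on an assumed difference in effect size of 0.1 between the interventions", and gives the source: "This is the average ES found between two active preventive interventions with anxious youth". For the symptom scale, "a SD of 14 will be applied for the SCAS-c/p post-intervention scores" and "With a difference in ES = 0.1, a non-inferiority bound is set to 1.4". For CALIS, with an SD of 7, "the non-inferiority bound is set to 0.7". Each measure is tested one-sided at 0.025 on the post-intervention score, and three of the four measures (SCAS and CALIS, youth and parent) must pass.

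The Power calculation section contains one calculation, introduced as "Power calculations for differences among the three conditions": 294 participants for an effect size of 0.40 at 80% power and alpha 0.05, raised to 323 for 10% attrition. The choice of 0.40 is defended by the effect expected against the waitlist.

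The Study design section adds: "Those allocated to the waitlist group will be randomized a second time to either VAAG or CHILLED after a delay of 10 weeks". The Non-inferiority section and the Data analytical plan do not say whether these participants enter the comparison of the two programmes.

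**The concern.** A non-inferiority margin should be the largest loss of effect one would accept in exchange for the shorter programme. Here its stated basis is the difference typically found between two active programmes, which describes past results and does not by itself say what loss is tolerable.

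The margin is also a quarter of the effect used for the sample size (0.1 against 0.40). Required sample size grows with the inverse square of the distance to be resolved, so a trial sized for 0.40 is about 16 times too small for a margin of 0.1, even with no true difference.

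At stake is the trial's second research question. If non-inferiority is unlikely to be shown even for equally effective programmes, failing to show it says little about VAAG. The text does not say how such a failure would be interpreted.

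**Working it through.** **Inputs from the protocol article.** Margin 1.4, SD 14 (0.1 SD); CALIS 0.7, SD 7 (also 0.1 SD); one-sided alpha 0.025; three-of-four rule (Non-inferiority). N = 294, effect size 0.40, power 0.80, alpha 0.05, correlation 0.6 between two measurements (Power calculation). Equal allocation to three conditions (Enrollment and randomization), so 294/3 = 98 per arm. Waitlist later split between the programmes (Study design), so up to 98 + 49 = 147 per arm if pooled.

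**Assumptions of this check.** Correlation between the four test statistics 0.3-0.7; for clustering, ICC 0.02-0.05 with groups of 6.5. The protocol gives neither.

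**1. The plan's own figure.** Two-group formula: n = 2 × ((1.96 + 0.842)/0.40)² = 98.1 per arm, and 3 × 98.1 = 294.3. A three-group repeated-measures F test (two measures, r = 0.6, f = 0.40/√6 = 0.163) gives 294 exactly. Recruitment: 294 × 1.10 = 323.4. The figure reproduces as a superiority sizing at 0.40.

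**2. What must be observed to pass.** SE = 14 × √(2/98) = 2.0, so the 95% CI half-width is 3.92. The upper limit must not exceed 1.4, so the observed difference (VAAG minus CHILLED) must be at most 1.4 − 3.92 = −2.52. VAAG must look about 2.5 SCAS points better.

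**3. Power per outcome if the programmes are identical.** Power = Φ(0.1/SE − 1.96), with SE in SD units = √(2v/n); v = 1 unadjusted, v = 1 − 0.6² = 0.64 baseline-adjusted.

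| Analysis | SE | Power |
|---|---|---|
| 98 per arm, unadjusted | 0.143 | 10.4% |
| 98 per arm, adjusted | 0.114 | 13.9% |
| 147 per arm, unadjusted | 0.117 | 13.5% |
| 147 per arm, adjusted | 0.093 | 18.7% |

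**4. Three-of-four rule, identical programmes** (simulated correlated normal statistics, correlations 0.3 to 0.7): 2.1-5.7% at 98 per arm unadjusted; 6.2-12.1% at 147 per arm adjusted.

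**5. If VAAG is truly worse by 0.1 SD.** The truth lies on the margin: Φ(0 − 1.96) = 2.5% per outcome at any sample size.

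**6. Clustering.** Design effect 1 + 5.5 × ICC = 1.11 to 1.275. The 10.4% becomes 9.8% to 9.0%; the 18.7% becomes 17.3% to 15.6%.

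**7. What 80% power per outcome would take, ignoring clustering.** With no true difference: n = 2 × (1.96 + 0.842)²/0.1² = 1,570 per arm, or × 0.64 = 1,005 adjusted. At 98 per arm unadjusted, VAAG would have to be truly better by 2.802 × 0.143 − 0.1 = 0.30 SD.

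**The case against.** The strongest reply is that a narrow margin is conservative: it does not raise the risk of wrongly declaring VAAG non-inferior, and the waitlist contrast, which is the first aim, is untouched. Both points are right. They limit the harm to an objective that will probably go unanswered, but they do not make it answerable.

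The assumed 0.1 can also be read as a tolerated difference benchmarked on earlier comparisons, rather than a forecast that VAAG will be 0.1 SD worse. The Objectives section hopes that self-help will offset some loss of effect. A reader might infer that the trial has only 2.5% power under its own assumption, but the text does not settle that, and 2.5% applies to any such test when the truth sits on its margin. The 2.5% is therefore conditional. The 10% figure does not depend on this reading.

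A reader might also infer that the test fails whatever the truth. It does not: if VAAG were really 0.30 SD better, power per outcome would be about 80%. Nor is 10% the power of the whole objective, since the three-of-four rule makes that lower.

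This is a condensed article, and a fuller document may contain a non-inferiority sizing. One can say only that none is shown. But the margin, alpha, decision rule and sample size are all fixed here, so their incompatibility is not a detail left to an analysis plan. No passage equates a failed test with inferiority, so that misreading is a risk rather than something the plan states.

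Finally, the abstract gives 0.8 for the interference scale against 0.7 in the Non-inferiority section. These must be reconciled, but 0.8 raises CALIS power only to 12.3% with identical programmes at 98 per arm.

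**Conclusion.** The concern holds. The margin of 0.1 SD is taken from an average of past differences without being justified as an acceptable loss, and the only sizing shown is for three conditions at 0.40. If the programmes are identical, power per outcome is about 10% (98 per arm, unadjusted), 14% with baseline adjustment at r = 0.6, and 19% with the re-randomised waitlist also pooled. For the objective as defined by the three-of-four rule it is about 2-6%, or 6-12% in the most favourable of these analyses.

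The result rests on the protocol's SDs, margins and alpha, equal arms, and the assumed correlations between measures. Group randomisation is ignored in these figures; at the assumed ICCs it lowers them slightly. No combination examined comes near the usual 80% unless VAAG is materially better than CHILLED, so a failed non-inferiority test would be close to uninformative.

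**What to change.** 1. In the Power calculation section, state that 323 was sized for the three-condition contrast at 0.40, and give the non-inferiority power per outcome and for the three-of-four rule.
2. Replace the raw post-score comparison with a baseline-adjusted comparison of everyone randomised to VAAG or CHILLED. Include the re-randomised waitlist groups, with their post-wait score as baseline and a term for phase, and allow for group clustering.
3. Make the 95% confidence interval for VAAG minus CHILLED the main result, and commit in advance that an interval crossing the margin is inconclusive and not evidence of inferiority.
4. Stop presenting the average difference between active programmes as the basis for the margin unless 0.1 SD is separately justified as an acceptable loss.

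The cost is wording and a modest change to the model. No extra participants are needed, which matters because the Trial status section reports 310 already randomised. These changes improve precision and interpretation but do not bring power to a conventional level. The stated ability to show non-inferiority will look less favourable, and pooling assumes that the VAAG-CHILLED difference is similar after the waiting period.

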#### Data analytical plan

Data will be collected electronically. The effects of the two active interventions compared to the WLC will be analyzed by mixed effect models. The predictive value of the various pre-treatment characteristics will be evaluated using regression analyses. The test for non-inferiority will be performed for the primary outcome variables, followed by superiority analyses, including both primary and secondary outcome measures. Analysis will be performed according to an intention-to-treat procedure. Missing data will be handled by multiple imputations. Further details about the protocol are reported in the SPIRIT checklist (Additional file 2: Table S1).

## Discussion

Prevention and early intervention approaches to anxiety disorders are important, as young people often experience barriers toward seeking mental health services. The present study will provide information about the efficacy of school-based CBT interventions for anxious youth. If they are found to be effective, these interventions could be subject to large-scale implementation in school health services. The study extends previous studies on early intervention for anxious youth by comparing two programs with different intensity. The brief intervention may be easier to implement in schools as it requires less time and professional resources, but needs first to be found non-inferior to the more intense intervention. In the present study, psychometrically sound measures are applied with multiple informants in a randomized controlled design. The interventions are studied with conditions that closely match real-world implementation. The use of diagnostic interviews and blind evaluators of treatment gains was, however, not feasible with the resources available and would also not be in accordance with the school health services as they are usually being provided.

### Trial status

Recruiting. Inclusion of participants started in October 2014. By November 2016, 310 adolescents have been included and randomized into the study. Inclusion will be finished by December 2016 and data collection by March 2018.

## Abbreviations

CALIS: Children Anxiety Life Interference Scale
CATS: Children’s Automatic Thought Scale
CBT: Cognitive Behavioral Therapy
CEQ: Credibility and Expectancy Questionnaire
CGI: Clinical Global Impression Scale
CGSQ: Caregiver Strain Questionnaire
DASS: Depression, Anxiety and Stress Scale
ES: Effect Size
GSE: General Self-Efficacy Scale
KINDL: Kinder Lebensqualität Fragebogen
LE: Life-Event scale
LI-CBT: Low-Intensity CBT
PF: Psychological First Aid kit
RCT: Randomized Controlled Trial
READ: Resilience Scale for Adolescents
SCAS: Spence Children’s Anxiety Scale
SDQ: Strength and Difficulties Questionnaire
SMFQ: Short Mood and Feeling Questionnaire
WLC: Waitlist Control Group
YES: Youth Engagement in and between Sessions
